### Randomization

Randomization procedures will be conducted strictly before PPCI. Eligible patients will be randomized 1:1 to the PCSK9 inhibitor group or the control group and stratified by age (≤ 60/>60; 2 categories), gender (female/male; 2 categories), time from symptom onset (< 3/3–24 h; 2 categories) using the interactive web response system (IWRS) after providing written informed consents.

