### Study endpoints

The primary endpoint is MSI measured by CMR at 1 week after the index PPCI. The secondary endpoints are the peak time of CK-MB and TnI/TnT after PPCI; the postoperative fall time of the ST segment on ECG; the rate of plasma LDL-C compliance (< 1.4 mmol/L and a reduction of >50% from baseline) at 1, 3, and 6 months after PPCI; infarct size and EF measured by CMR at 6 months after PPCI; the occurrence of MACE.

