### Sample size calculation

Referring to our prior small sample size study, the MSI was higher in the PCSK9 inhibitor group (mean: 0.50; standard deviation [SD]: 0.16) than in the control group (mean: 0.41; SD: 0.15). To guarantee 90% power of the study at a significance level of 0.05, at least 64 patients per group will be needed. Considering a dropout rate of 20%, the required sample size is 160 (80 patients in each group). PASS 15 was used to calculate the sample size.

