### Statistical analysis

Continuous variables (including the primary endpoint) will be expressed as mean (SD) or median (interquartile rage) and will be compared using the *t*-test or the Mann-Whitney *U* test, as appropriate. Categorical variables will be expressed as counts and percentages and compared using the χ2 test or Fisher's exact test, as appropriate. We plan to assess the consistency of the treatment effect on the primary endpoint among three pre-specified subgroups that will be analyzed individually and then in a multivariate model. The following subgroup analyses are planned: age: < 60 years vs. ≥60 years; sex: female vs. male; duration from symptom onset to study drug infusion: < 3 h vs. 3–24 h. Safety analyses will include tabulation of the type and frequency of all adverse events and severe adverse events. All primary and secondary endpoints will be analyzed on an intention-to-treat basis (all patients will be analyzed as part of their designated treatment group) and protocol-based premise (analyses will only be performed as part of their designated treatment group when the patient received their designated treatment). For the intention-to-treat analysis, all patients who have provided written informed consent and who have been randomized in the study will be included in the analysis sample, regardless of whether they have received the correct treatment or whether there is crossover. For the protocol-based analysis, only registered patients who received the specified treatment will be included in the analysis sample. Patients who are lost to follow-up will be eliminated at the time of the last known contact. *P* values and confidence intervals will be two-sided with a significance level of 0.05.

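### The primary MSI test omits the three randomisation strata: a valid but conservative analysis that forgoes a little precision if those factors predict MSI

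*Protocol article*

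**What the plan says.** The Study endpoints section fixes the outcome: "The primary endpoint is MSI measured by CMR at 1 week after the index PPCI". It is continuous.

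The Randomization section states that "Eligible patients will be randomized 1:1 to the PCSK9 inhibitor group or the control group", with allocation "stratified by age (≤ 60/>60; 2 categories), gender (female/male; 2 categories), time from symptom onset (< 3/3–24 h; 2 categories". Three two-level factors give 2 × 2 × 2 = 8 strata.

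The Statistical analysis section opens with "Continuous variables (including the primary endpoint) will be expressed as mean (SD) or median (interquartile rage" and goes on to say that they "will be compared using the *t*-test or the Mann-Whitney *U* test, as appropriate". The primary endpoint is named in that sentence, so this is the stated primary comparison. It contains no stratum term.

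The only model in the section concerns consistency of the treatment effect across "three pre-specified subgroups that will be analyzed individually and then in a multivariate model". It is not the primary test.

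**The concern.** Stratified allocation makes the arms nearly equal in their mix of age, gender and onset time. Whatever part of MSI those factors explain then contributes little to the chance difference between arms. A two-sample test does not know this. It estimates its standard error from the full within-arm spread, which still includes the differences between strata. If the factors are prognostic, that standard error is larger than the true sampling error of the difference.

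The p-value then tends to be too large and the interval covers more than 95%. The sponsor pays for stratification in the design and does not collect the precision in the analysis. Only efficiency is at stake: the error runs in the safe direction and does not make a false positive more likely.

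**Working it through.** **Inputs.** From Sample size calculation: "the MSI was higher in the PCSK9 inhibitor group (mean: 0.50; standard deviation [SD]: 0.16") "than in the control group (mean: 0.41; SD: 0.15"); 90% power; significance level 0.05; 64 evaluable patients per group; 20% dropout, hence 80 per group. From Statistical analysis: two-sided testing. R2, the share of MSI variance explained by the strata, is not in the documents and is assumed at 0, 0.05, 0.10 and 0.20.

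**Step 1: reproduce the plan's figure.** Difference d = 0.50 − 0.41 = 0.09. SD = √((0.16² + 0.15²)/2) = 0.1551. Normal approximation: n = 2(1.960 + 1.282)² × 0.1551²/0.09² = 62.4, so 63 per group. The noncentral t calculation gives 64, with power 90.3%. Dropout: 64/0.80 = 80 per group, 160 in total. The stated figures reproduce.

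**Step 2: effect of ignoring the strata, exact balance.** With 64 per group the unadjusted test uses SE = 0.1551 × √(2/64) = 0.0274, so d/SE = 3.283. If the strata are exactly balanced, the true standard error is 0.0274 × √(1 − R2). Hence:

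- type I error of the unadjusted test = 2[1 − Φ(1.96/√(1 − R2))]
- power, unadjusted = Φ((3.283 − 1.96)/√(1 − R2))
- power, adjusted = Φ(3.283/√(1 − R2) − 1.96)

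For R2 = 0.10, √0.90 = 0.9487. Type I error is 2[1 − Φ(2.066)] = 3.9%. Unadjusted power is Φ(1.394) = 91.8% and adjusted power is Φ(1.500) = 93.3%. The unadjusted interval is wider than the adjusted one by 1/0.9487 − 1 = 5.4%.

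**Step 3: allow for the planned dropout.** If patients are lost at random, the numbers left in each stratum and arm vary again. A 20% loss restores about a fifth of the between-stratum variation in the contrast. The factor 1 − R2 becomes 1 − 0.8 × R2. For R2 = 0.10: 1.96/√0.92 = 2.043, type I error 4.1%. For R2 = 0.20: 1.96/√0.84 = 2.139, type I error 3.2%.

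**Step 4: simulation.** 160 randomised, 8 strata, 20% random dropout, d = 0.09 for power. Block size and stratum prevalences are not in the documents and had to be assumed.

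| Assumed R2 | Type I, exact balance (formula) | Type I, 20% dropout (formula) | Type I, 20% dropout (simulated) | Power unadjusted vs adjusted, exact balance (formula) | Power unadjusted vs adjusted, 20% dropout (simulated) |
|---|---|---|---|---|---|
| 0 | 5.0% | 5.0% | – | 90.7% vs 90.7% | – |
| 0.05 | 4.4% | 4.5% | 4.7% | 91.3% vs 92.1% | 90.8% vs 91.3% |
| 0.10 | 3.9% | 4.1% | 3.9% | 91.8% vs 93.3% | 91.4% vs 92.9% |
| 0.20 | 2.8% | 3.2% | 3.7% | 93.0% vs 95.6% | 92.0% vs 95.3% |

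Two further simulations with dropout gave 4.1% at R2 = 0.10 in both, and 3.5% and 3.1% at R2 = 0.20. In a run of 6,000 trials the Monte Carlo standard error at 3.5% is √(0.035 × 0.965/6000) = 0.24 points, so much of this spread is noise. About 3.5% is a fair central value at R2 = 0.20.

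Simulated power forgone with dropout: 91.3 − 90.8 = 0.5, 92.9 − 91.4 = 1.5 and 95.3 − 92.0 = 3.3 points. All of this is for the t-test; the Mann-Whitney branch was not computed.

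**The case against.** The strongest reply is that no promise of the protocol fails. Type I error stays at or below 5%, coverage at or above 95%, and the planned test still reaches about 90% power at 64 per group. This stands, and it is why the point is minor. A reader might infer that the p-value is invalid, the trial underpowered or the sample size wrong; the protocol's own figures contradict all three.

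Second, the size depends wholly on R2. The documents report no association between MSI and age, gender or onset time. Choosing the factors for stratification and again for subgroups suggests that the sponsor thinks them relevant, but that is not a measurement. This also stands: the loss is conditional and is zero if the factors do not predict MSI.

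Third, a condensed article leaves detail to a statistical analysis plan, and a multivariate model is already mentioned. This does not remove the point. The article names the test for the primary endpoint, and the model it mentions serves subgroup consistency.

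Three extensions are tempting, but the stratification argument does not support them:

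- **Centre.** Randomization does not list centre as a stratification factor, so omitting it causes no mismatch of this kind.
- **Choice between t-test and Mann-Whitney.** The rule for choosing is a separate matter that an article may leave to the analysis plan.
- **Adjusted models for 6-month infarct size and ejection fraction.** No loss has been shown for those endpoints.

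**Conclusion.** The mismatch is in the text: three stratification factors in the design, none in the stated primary test. If those factors predict MSI, the test is valid but conservative and inefficient.

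The type I error and power ranges rest on an assumed R2 of 0.05 to 0.20, blocks of four within strata, assumed stratum prevalences and dropout unrelated to outcome or arm. On the same R2 range, the unadjusted interval is about 3% to 12% wider than the adjusted one (1/√0.95 = 1.026; 1/√0.80 = 1.118). The direction is certain given a prognostic stratum effect; the size is not. Severity is minor, and the sample size needs no change.

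**What to change.** In Statistical analysis, name one primary analysis: a linear model of 1-week MSI on treatment and the three stratification factors, reporting the adjusted mean difference with its 95% confidence interval. Enter the factors as used at randomisation: age ≤ 60 or > 60, gender, and onset < 3 h or 3–24 h. This needs saying because the subgroup list cuts age at < 60 or ≥ 60 and measures time to study drug infusion, so those variables are not the randomisation factors.

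Keep the unadjusted t-test and a rank test (Mann-Whitney, or van Elteren if stratified) as sensitivity analyses.

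The cost is a few sentences and three degrees of freedom, from 126 to 123 with 128 evaluable patients. The factors are already recorded at randomisation, so no new data or patients are needed. Adding centre, or adjusting the secondary endpoints in the same way, is optional.

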We recently conducted a randomized pilot study (PERFECT trial, NCT04731105) in 20 patients with anterior myocardial infarction accompanied by chest pain that began within 24 h. In this study, a single 75-mg dose of alirocumab was subcutaneously injected immediately after PPCI and lead to a trend toward an increase in the myocardial salvage index (MSI) compared with the control group (0.50 ± 0.16 vs. 0.41 ± 0.15; *p* = 0.21).

To further confirm the results of the PERFECT trial, we designed this multicenter, randomized controlled study to investigate whether early application of alirocumab in patients with STEMI can increase the MSI 1 week after injection and decrease the infarct size 6 months later. The MSI, as assessed by cardiac magnetic resonance imaging (CMR) with late gadolinium enhancement, is considered to be the gold-standard method to assess of infarct size (13). Thus, we will use the MSI, instead of infarct size, as the primary endpoint in this study.

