## Discussion

Although early revascularization by PPCI is essential for myocardial myocardium, large infarctions frequently occur in patients with STEMI. Consequently, mortality remains high, and many patients develop complications, such as heart failure, after STEMI. Local and severe sterile inflammation is one of the main causes of ischemia–reperfusion injury (17). Despite some prior studies not meeting the expected goals (18–20), depressing inflammation directly or indirectly in the early stage of STEMI is a feasible strategy to protect the myocardium and limit infarct size to improve outcomes.

PCSK9 mainly regulates the concentration of LDL-C by degrading the LDLR; thus, PCSK9 inhibitors have become a novel effective therapeutic strategy for lipid management in patients with hypercholesterolemia and ACS. Recent studies have indicated that PCSK9 also plays a role in inflammation. PCSK9 also mediates cardiomyocyte autophagy (8) and aggravates inflammation through the Toll-like receptor 4/nuclear factor-κB (21) and lipoprotein receptor-related protein 1 (22) pathways. Conceivably, PCSK9 may be a new target for the treatment of AMI. Recent studies have shown that PCSK9 inhibitors can reduce cardiovascular events and attenuate the risk of type 2 MI in patients with ACS (23, 24). Thus, early application of PCSK9 inhibitors may be an effective treatment strategy for patients with STEMI.

In the PERFECT II trial, we expanded the sample size, inclusion criteria, and the number of clinical centers on the basis of the PERFECT trial. Therefore, the PERFECT II trial will provide better evidence on the impact of early application of the PCSK9 inhibitor alirocumab on MSI and ventricular remodeling in patients with STEMI after PPCI.

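### Effect and SD come from an anterior-only pilot, but the trial enrols STEMI of any location and infarct location is in neither the MSI comparison nor the listed subgroups

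*Protocol article*

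**What the plan says.** The protocol article (Introduction) describes the pilot as a randomised study in "20 patients with anterior myocardial infarction accompanied by chest pain that began within 24 h" and reports MSI in the alirocumab arm "compared with the control group (0.50 ± 0.16 vs. 0.41 ± 0.15"), p = 0.21. PERFECT II is presented as the study meant to confirm that result.

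Sample size calculation uses the same figures: "Referring to our prior small sample size study, the MSI was higher in the PCSK9 inhibitor group" ("mean: 0.50; standard deviation [SD]: 0.16"), against a control mean of 0.41 and SD of 0.15. This gives 64 per group for 90% power and 160 in total after 20% dropout.

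Table 1 admits STEMI within 24 h of onset, with no limit on infarct location. The Discussion acknowledges the widening: "we expanded the sample size, inclusion criteria, and the number of clinical centers on the basis of the PERFECT trial".

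Randomization is stratified by age, gender and time from symptom onset. Under Statistical analysis, continuous variables, expressly including the primary endpoint, are compared by t-test or Mann-Whitney U test. Consistency of the effect is to be assessed "among three pre-specified subgroups that will be analyzed individually and then in a multivariate model", and the three are then named: age, sex and time from onset. Location is not mentioned. Table 2 schedules electrocardiography and coronary angiography before the operation.

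**The concern.** Of the pilot's entry conditions that the article reports, the 24-hour window is kept and the anterior location is dropped. The effect and SD are carried over to the wider population without comment. Two consequences follow.

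- **Spread.** An SD observed in anterior infarcts alone contains no between-location variation. If mean MSI differs by location, the SD in the mixed population is larger than assumed, and an unadjusted comparison bears that cost.
- **Interpretation.** If the overall result is weak, the first question will be whether the pilot effect held in anterior infarction. Any answer would come from an analysis chosen after the data were seen, in an open-label trial.

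This is not merely a detail left for a statistical analysis plan. The article states the test for the primary endpoint and gives a closed list of three subgroups.

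**Working it through.** **Inputs from the article.** Difference 0.50 − 0.41 = 0.09; SDs 0.16 and 0.15; two-sided alpha 0.05; 90% power; 64 evaluable per group; 20% dropout.

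**Inputs not in the article (assumed).** Anterior share 40% to 60%; gap in mean MSI between locations 0 to 0.15; effect outside anterior infarction 0 to 0.05.

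**1. The plan's own figure.** Root-mean-square SD = √[(0.16² + 0.15²)/2] = √0.02405 = 0.1551. With the noncentral t distribution, 63 per group gives 89.8% power and 64 gives 90.3%. Then 64/0.8 = 80 per group, 160 in total. The stated numbers reproduce exactly. With an assumed 10 per arm, the pilot p-value also reproduces (t = 1.30, p = 0.21).

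**2. What adjustment is worth if 0.1551 is a within-location SD.** This is what an anterior-only pilot implies. With anterior share p and location gap g, total SD = √[0.02405 + p(1 − p)g²]. At p = 0.5 and 64 per group:

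| Gap g | Total SD | Power, unadjusted | Power, adjusted |
|---|---|---|---|
| 0 | 0.1551 | 90.3% | 90.3% |
| 0.05 | 0.1571 | 89.6% | 90.3% |
| 0.10 | 0.1629 | 87.3% | 90.3% |
| 0.15 | 0.1723 | 83.5% | 90.3% |

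At p = 0.4 the unadjusted figures are almost the same (89.6%, 87.4% and 83.8% for the three non-zero gaps). The gain runs from nothing to about 7 percentage points.

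**3. What an estimate by location would show.** Anterior patients per group = 64p, and the half-width of the 95% CI = 1.96 × 0.1551 × √[2/(64p)].

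| Anterior share | Anterior per group | CI half-width | Power at 0.09 (normal approximation) |
|---|---|---|---|
| 40% | 25.6 | 0.085 | 55% |
| 50% | 32 | 0.076 | 64% |
| 60% | 38.4 | 0.069 | 72% |

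Interaction at p = 0.5: SE = 0.1551 × √(2/32 + 2/32) = 0.0548. If the effect elsewhere is 0.05, the contrast is 0.04 and power is Φ(0.04/0.0548 − 1.96) = Φ(−1.23), about 11%. If the effect elsewhere is 0, power is Φ(0.09/0.0548 − 1.96) = Φ(−0.32), about 38%.

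**4. Dilution, kept separate.** If half the patients are non-anterior with an effect of 0.05, the average effect is 0.5 × 0.09 + 0.5 × 0.05 = 0.07, and overall power at 64 per group is 71.7%. This follows from the assumed effect and the broad eligibility. A location term in the model does not bring the average back to 0.09.

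**The case against.** The case against is substantial, and much of it stands.

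- **No documented link.** Nothing in the article shows that location predicts MSI, infarct size or EF. This stands, so the range must include zero gain.
- **The unadjusted test is valid.** Its type I error already allows for chance imbalance, and the stated objective concerns patients with STEMI in general, which a randomised comparison answers. This stands; the point is about efficiency and interpretation, not validity.
- **A reader might infer that adjustment lifts power above 90%**, to 91.7%, 93.0% or 95.4% if location explains 5%, 10% or 20% of the variance. Those figures shrink the pilot SD by √(1 − R²). An anterior-only SD already excludes between-location variance, so this removes it twice. Adjustment then only restores about 90.3%.
- **A reader might infer that leaving out location causes the 71.7% power.** It does not. That figure comes from an assumed smaller effect, which neither a covariate nor a subgroup recovers.
- **A reader might infer that the trial cannot test whether the pilot result holds.** That is too strong. ECG and angiography precede the operation, so location should be obtainable and could be examined later. What is missing is a prespecified analysis.
- **The interaction test is weak.** This stands: 11% to 38% power makes the subgroup an exploratory estimate only.
- **Covariates belong in an analysis plan that is not shown.** This stands in part. The content of the multivariate model is not described, and that is no finding. The test for the primary endpoint and the list of three subgroups are stated outright.

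It also cannot be said that location is the only difference between the two populations, because the pilot's full criteria are not given.

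**Conclusion.** The point holds in a limited form. The effect and SDs come from anterior infarction, the trial enrols any location, and the stated analysis of MSI neither adjusts for location nor prespecifies an estimate by location. The sample size is not wrong on its own inputs, and the planned test is valid.

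The benefit of adjusting is conditional. It is nil if location is unrelated to MSI, and about 0.7 to 7 percentage points of power (89.6% to 83.5%, restored to 90.3%) for location gaps of 0.05 to 0.15. This assumes that the pilot SD is within-location, that about half the infarcts are anterior, and that 64 per group are evaluable. The estimate by location would be imprecise, with CI half-widths of 0.069 to 0.085 in the anterior group. Its value is that it is fixed before the data are seen. The change is worth making because it is nearly free, not because the trial fails without it.

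**What to change.** Replace the unadjusted comparison of MSI, 6-month infarct size and 6-month EF with a linear model containing treatment, the three stratification factors as used at randomisation, and infarct location (anterior or non-anterior, from the pre-operation ECG or angiogram). Prespecify the treatment effect by location, with a confidence interval and an interaction term, and label it exploratory. Leave the strata and the sample size unchanged.

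The cost is a short amendment to the analysis text before any outcome data are examined. It needs no new procedure, because the ECG and angiogram are already scheduled. The downsides are a slightly more complex model for three endpoints and one more exploratory comparison.

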### Ethics and dissemination

This trial has been approved by the ethics committee of Tongren Hospital, Shanghai Jiao Tong University School of Medicine (2022-006-01). The study protocol and informed consent prior to patient participation will be approved by the ethics committee. No changes to the protocol or informed consent will be allowed without the approval of the ethics committee. As required by the ethics committee, the investigator will report the progress of the study until completion. Additionally, any protocol amendments and associated informed consent changes will be submitted to the ethics committee and must be approved in writing prior to implementation. Enrolled patients can withdraw from the trial at anytime during the process of the study. The privacy of patients will be strictly maintained during and after the study. Questions related to privacy and secrecy are listed in the informed consent form. All data will only be accessed by the study staff and will be kept strictly confidential. In addition, the data will be protected in locked cabinets at the participating clinical centers. An independent data monitoring committee (IDMC) will review the security data, including data on death, myocardial infarction, stroke, and other adverse events. The IDMC has the right to recommend suspension of enrollment or termination of the research based on safety considerations. The executive committee will make a final decision on the early termination of the study based on the recommendations.

The results will be disseminated at several research conferences and as published articles in peer-reviewed journals after approval from the study sponsors.

## Discussion

Although early revascularization by PPCI is essential for myocardial myocardium, large infarctions frequently occur in patients with STEMI. Consequently, mortality remains high, and many patients develop complications, such as heart failure, after STEMI. Local and severe sterile inflammation is one of the main causes of ischemia–reperfusion injury (17). Despite some prior studies not meeting the expected goals (18–20), depressing inflammation directly or indirectly in the early stage of STEMI is a feasible strategy to protect the myocardium and limit infarct size to improve outcomes.

PCSK9 mainly regulates the concentration of LDL-C by degrading the LDLR; thus, PCSK9 inhibitors have become a novel effective therapeutic strategy for lipid management in patients with hypercholesterolemia and ACS. Recent studies have indicated that PCSK9 also plays a role in inflammation. PCSK9 also mediates cardiomyocyte autophagy (8) and aggravates inflammation through the Toll-like receptor 4/nuclear factor-κB (21) and lipoprotein receptor-related protein 1 (22) pathways. Conceivably, PCSK9 may be a new target for the treatment of AMI. Recent studies have shown that PCSK9 inhibitors can reduce cardiovascular events and attenuate the risk of type 2 MI in patients with ACS (23, 24). Thus, early application of PCSK9 inhibitors may be an effective treatment strategy for patients with STEMI.

In the PERFECT II trial, we expanded the sample size, inclusion criteria, and the number of clinical centers on the basis of the PERFECT trial. Therefore, the PERFECT II trial will provide better evidence on the impact of early application of the PCSK9 inhibitor alirocumab on MSI and ventricular remodeling in patients with STEMI after PPCI.

